### Participants

We will recruit through local ASD support groups, online social media, and noticeboard advertisements (eg, at Federation University Australia). We will also use snowball recruiting to better penetrate the ASD community. Participants with an ASD (based on the assessments described in the Assessment section) will be assigned to the ASD group. Other participants will be assigned to the alexithymia-matched general population group (AM group).

The researchers will also use the 20-item Toronto Alexithymia Scale (TAS-20) total scores [40] to match the ASD group with the AM group without an ASD. Specifically, the number of participants in each group meeting criteria for alexithymia will be matched as indicated by TAS-20 scores ≥61, which is how groups have been matched in similar studies (eg, [32]).

The inclusion criterion is that participants are 18 years of age and older. The ASD group also has the added inclusion criterion of a confirmed ASD based on the assessment described in the Assessment section. Exclusion criteria include the participant having another mental health condition (other than an ASD if in the ASD group) diagnosed by a clinician and that the Kessler Psychological Distress Scale (K10) [41] indicates a significant level of distress (cut-off score of 22).

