### Assessments

The main aim of the current study is to assess the efficacy of the intervention in the general population and an ASD population, but also if people with high levels of alexithymia gain additional benefit. Further, this study will aim to replicate the study by Cook et al [32], which suggested that alexithymia, not ASD, predicts poor FEER. This requires having a general population group and another group with people with ASD, with both groups being matched on levels of alexithymia. Therefore, participants will be prescreened online to facilitate creating this composition of participants. During the online screening stage, participants will choose to consent in the study, complete the TAS-20, and indicate if they have an ASD or if they have been diagnosed with an ASD. During this screening stage, participants will also complete demographic information, the Autism Spectrum Quotient (AQ-10) [42], and the K-10.

Participants will then be invited to a clinical interview with a provisional psychologist (PP) at the Federation University Psychology Clinic who will confirm a reported diagnosis of ASD and complete an observational assessment that gives a diagnostic indication of an ASD. Participants who have reported a diagnosis will be asked what instrument was used and if the PP can request a copy of the results. The PP will also complete the Autism Mental Status Exam 2.2 (AMSE) [43,44]. The AMSE is an 8-item observational assessment that takes place during a clinical interview and predicts ASD classification on the Autism Diagnostic Observation Schedule (ADOS) [45]. During this clinical interview, participants will also be administered the Depression Anxiety Stress Scales-21 (DASS-21) [46] and the Wechsler Abbreviated Scale of Intelligence (WASI-II) [47] to assess depression, anxiety, and IQ, which will be used as control variables in the analyses of the results.

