#### TAS-20

The 20-item TAS-20 [40] is the most widely used measure of alexithymia. It consists of 20 items, with each item being rated on a 5-point Likert scale between “strongly disagree” (1) and “strongly agree” (5). Higher scores designate higher degrees of alexithymia with a possible score ranging between 20 and 100. Cut-off scores have been developed with scores ≤50 suggesting no alexithymia, scores between 51 and 60 indicating borderline alexithymia, and scores ≥61 suggesting alexithymia [50]. The TAS-20 has been demonstrated to be a valid and reliable measure of alexithymia [40] with an internal consistency of α=.81 and test-retest reliability of .77 (*P*<.01).

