### Statistical Analyses

The data will be analyzed using SPSS, Version 25. Alexithymia will be analyzed to aid in matching the AM group and ASD group on alexithymia. To ensure that the ASD and AM groups, and also the experimental and control groups, are comparable, means and standard deviations of participant characteristics will also be compared with tests of difference.

The study design is a mixed factor, 2x2x2, within-between design (see Table 2), and therefore, the most appropriate test of difference is a mixed factorial ANOVA, set up according to Table 2 with IQ, depression, and anxiety variables added as covariates. This will provide analyses of whether the instructed mimicry intervention task was effective by comparing baseline scores to posttest scores. Additionally, it will provide the ability to compare posttest scores between the control group and the intervention group. Finally, this analysis will have the additional ability to discern these differences based on group (ASD group and AM group).

In addition to the mixed factorial ANOVA, a hierarchical regression analysis will also be conducted (see Table 3) to determine the predictive ability of alexithymia on the primary outcome variable.

**Table 2 table2:** Experimental group and intervention design.

Time point	ASD^a^ group (n=~32)		AM^b^ group (n=~32)	
	Control task condition (n=~16)	Mimicry task condition (n=~16)	Control task condition (n=~16)	Mimicry task condition (n=~16)
Pretest	FEER^c^ task score	FEER task score	FEER task score	FEER task score
Posttest (the intervention task is the posttest)	FEER task score	FEER task score	FEER task score	FEER task score

^a^ASD: autism spectrum disorder.

^b^AM: alexithymia-matched general population.

^c^FEER: facial emotion expression recognition.

**Table 3 table3:** Hierarchal regression stages for analysis.

Stage	Variables
Stage 1	IQ, age, gender
Stage 2	+Autism
Stage 3	+Alexithymia
Stage 4	+Intervention

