## Discussion

This paper describes, to our knowledge, the first study to assess an instructed mimicry task to increase emotion recognition ability in people with alexithymia and ASD. Despite the formulation of the alexithymia hypothesis, very few studies have assessed the impact of alexithymia in interventions aimed at increasing social functioning and in particular, emotion recognition. Additionally, to our knowledge, no other study has explored the benefits of instructed mimicry on emotion recognition in people with ASD and alexithymia. This mixed factor, 2x2x2, within-between design will assess the efficacy of the instructed mimicry task to increase FEER. This study design will enable the assessment of baseline and improvement scores individually for people with and without ASD while controlling for levels of alexithymia. This will allow analyses of how this intervention uniquely benefits ASD without the interference of alexithymia, which is known to frequently co-occur in ASD [9]. If this task is successful at increasing emotion recognition, it could provide easily accessible training to those with ASD, alexithymia, and other disorders that typically have high rates of alexithymia such as schizophrenia [59].

One proposed benefit of this intervention for people with alexithymia and ASD is that the software does not require supervision. This will likely benefit these populations as they typically enjoy computer-based interaction rather than social interaction, as indicated by previous studies (eg, [60]). This has the added benefit of improving access to the task as it could be used on a home computer, which may eliminate a key barrier to treatment.

Despite the benefits of this task and study design, some limitations are present. First, matching the ASD and AM groups on levels of alexithymia improves our ability to exclude alexithymia as a contributing factor of emotion recognition accuracy. Unfortunately, it also means that other confounding factors may have been systematically introduced when matching on alexithymia. This limitation will make it difficult to attribute any benefits of the intervention task specifically to autism. Additionally, when comparing emotion recognition accuracy, it will limit our ability to suggest whether emotion recognition difficulties are related to ASD or to alexithymia, as per the alexithymia hypothesis.

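### Matching the count with TAS-20 ≥61 does not ensure equal alexithymia, and the ANOVA comparing ASD with AM has no alexithymia covariate, so the baseline comparison rests on that match alone

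*Protocol article*

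**What the plan says.** **The match.** Under Participants, "the number of participants in each group meeting criteria for alexithymia will be matched as indicated by TAS-20 scores ≥61". The TAS-20 section describes the scale: "Higher scores designate higher degrees of alexithymia with a possible score ranging between 20 and 100", with "scores ≤50 suggesting no alexithymia, scores between 51 and 60 indicating borderline alexithymia, and scores ≥61 suggesting alexithymia". The Assessments section says the replication aim needs the two groups to be matched on levels of alexithymia.

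**The group comparison.** Under Statistical Analyses, the mixed factorial ANOVA is "set up according to Table 2 with IQ, depression, and anxiety variables added as covariates". The section adds that "this analysis will have the additional ability to discern these differences based on group (ASD group and AM group").

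**Alexithymia elsewhere in the plan.** Table 1 lists alexithymia, measured by the BVAQ at pretest, among the control variables. The Discussion says the design will assess baseline and improvement scores "for people with and without ASD while controlling for levels of alexithymia". Table 3 enters autism at Stage 2, alexithymia at Stage 3 and intervention at Stage 4. That regression is stated for the primary outcome variable, which the Primary Outcome section defines as an increase in FEER.

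**What is to be shown.** The second aim is that FEER relates to alexithymia and not to ASD. Two hypotheses concern baseline scores: that alexithymia predicts them negatively, and that the matched AM and ASD groups do not differ on them.

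**The concern.** A scale running from 20 to 100 is matched at one cut-point. On each side of that cut, the group drawn from the higher-scoring population tends to remain higher. The article gives reason to expect such a difference: the Abstract says alexithymia frequently co-occurs with ASD, and the Introduction puts severe alexithymia at up to 65% of adults with ASD.

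The ANOVA names its covariates, and alexithymia is not one of them. Any alexithymia gap left after matching therefore enters the ASD-v-AM contrast and can be read as an effect of ASD. The baseline comparison is the most exposed, because the one model that contains both autism and alexithymia is stated for a different outcome. What is at stake is the second aim, the separation of alexithymia from ASD.

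**Working it through.** **1. What the count match allows.** With equal counts on each side of the cut, the groups can differ by up to 60 − 20 = 40 points below it and 100 − 61 = 39 points above it. The match itself limits the gap only to about 39–40 points. How large it is likely to be depends on the source distributions, which the article does not give.

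**2. Expected gap under assumed distributions.** Take each source as normal with mean m and SD s, and let a = (60.5 − m)/s. Then:

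- mean above the cut ≈ m + s·φ(a)/(1 − Φ(a))
- mean below the cut ≈ m − s·φ(a)/Φ(a)
- group mean = p × (mean above) + (1 − p) × (mean below), with the same p in both groups because the counts are matched

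The results below also truncate at the ends of the scale (19.5 and 100.5), which changes little.

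Example: 60 v 50, SD 10, 16 of 32 above the cut (p = 0.5).

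- ASD: 0.5 × 68.30 + 0.5 × 52.34 = 60.32
- AM: 0.5 × 65.65 + 0.5 × 47.35 = 56.50
- Gap: 60.32 − 56.50 = 3.82 points, or 0.36 SD

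| Assumed source means, ASD v AM | Assumed SD | Share ≥61 in both groups | Gap, points | Gap, SD |
|---|---|---|---|---|
| 55 v 55 | 10–12 | 8, 16 or 21 of 32 | 0 | 0 |
| 58 v 52 | 10–12 | same | 2.0–2.6 | 0.17–0.27 |
| 55 v 48 | 12 and 11 | 32% | 2.9 | 0.24 |
| 60 v 50 | 10–12 | 8, 16 or 21 of 32 | 3.4–4.4 | 0.29–0.44 |
| 57 v 45 | 12 and 11 | 39% | 5.0 | 0.40 |
| 62 v 46 | 12 and 11 | 55% | 6.0 | 0.49 |
| 60 v 45 | 10–12 | 8, 16 or 21 of 32 | 5.0–7.2 | 0.41–0.68 |
| 65 v 45 | 10–12 | same | 6.9–8.9 | 0.56–0.84 |

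The 21 of 32 reflects the article's 65%. Where a percentage is shown, it is the share above the cut in the assumed ASD source.

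**3. Effect on the ASD contrast.** At an assumed alexithymia–FEER correlation of −0.4, a gap of 0.36–0.50 SD gives an apparent ASD deficit of 0.4 × 0.36 = 0.14 to 0.4 × 0.50 = 0.20 SD.

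The false-positive rate was simulated with 32 per group, 16 above the cut, SD 10, no true ASD effect, a slope of −0.3 to −0.5 SD per SD, and 6,000 runs:

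| Source means | No alexithymia term | Only the ≥61 indicator | Continuous TAS-20 |
|---|---|---|---|
| 55 v 55 | 3.1–4.1% | 4.8–5.1% | 4.8–5.0% |
| 60 v 50 | 6.6–9.1% | 7.5–12.8% | 4.9–5.0% |
| 60 v 45 | 9.1–16.8% | 10.4–23.9% | 4.8–5.1% |

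Adjusting for the matching indicator does not help. Adjusting for the continuous score does. The simulation leaves out the ANOVA's depression and anxiety covariates.

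**4. The planned balance check.** The plan compares group characteristics with tests of difference. With 32 per group, a two-sided 5% t test detects a true gap of 0.4 SD about 35% of the time, so a non-significant result says little about the match.

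**5. Sample size.** The stated 58 is reproduced as the overall regression test with the six predictors of Table 3 at f² = 0.27 (power 0.808). Stages 1–3 alone have five predictors and need 54. A single-degree-of-freedom term of that size at N = 58 has power 0.973 with six or seven predictors in the model. The proposed change does not disturb the sample size.

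**The case against.** - **No imbalance is shown.** A reader might infer that the match leaves the groups unequal and the comparison confounded. The article does not support that: it gives no TAS-20 means, and the expected gap is zero if the sources are alike. Both groups also exclude people with significant K-10 distress or another diagnosed condition, and online prescreening is used to build the matched sample. The calculation models none of this selection. This stands, and the point is limited to what the rule can leave.
- **Table 3 already separates the two.** From Stage 3 the autism coefficient is adjusted for alexithymia, so the stronger reading that neither model addresses the second aim is wrong. The aim's wording does not say baseline, and the hypothesis that alexithymia predicts baseline scores implies some model of them. An article may condense a second run of the regression. Even so, the text names the regression's outcome and the ANOVA's covariates, and as written they give no alexithymia-adjusted ASD-v-AM comparison at baseline.
- **Depression and anxiety are missing from Table 3.** The Assessments section says of depression, anxiety and IQ "which will be used as control variables in the analyses of the results", but not that every model must carry them, and the ANOVA does. Adding them to Stage 1 is a modelling preference and is not pressed here.
- **The bias is modest and partly absorbed.** If depression and anxiety correlate with alexithymia, those covariates take up some of the gap. At 0.14–0.20 SD, an unadjusted t test would reject only about 9–12% of the time. The bias would make ASD look worse, against the hypothesis of no difference, so it does not manufacture the predicted result. All of this is fair and keeps the point moderate.
- **The limitation is disclosed.** The Discussion warns that matching limits attribution to ASD or alexithymia. It gives the reason as other confounders brought in by matching, not alexithymia differences left after it.

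**Conclusion.** The point holds in a limited form. Equal counts at TAS-20 ≥61 do not guarantee equal alexithymia, and the ANOVA that compares ASD with AM omits the variable that Table 1 and the Discussion say is controlled. The baseline ASD-v-AM hypothesis therefore rests on the count match alone. For improvement, Table 3 already gives an autism coefficient adjusted for alexithymia.

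The size rests on assumed normal sources and assumed means: 0 points if equal, about 3 for 55 v 48, and about 5–6 for 57–62 v 45–46. Varying the ASD SD over 12–13 with an AM SD of 11 widens the last range to 4.4–6.5. The simulated false-positive rate reaches 9.1–16.8% in the widest case simulated, 60 v 45.

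The randomised mimicry-v-control comparison is not affected, because each diagnostic group is split equally between the tasks. The change is worth making, but this does not undermine the trial's first aim.

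**What to change.** 1. Add a continuous alexithymia score to the ASD-v-AM comparisons in the ANOVA: either the TAS-20 total or the BVAQ, which Table 1 already names as a control variable. State which one. Do not use the ≥61 indicator as the adjustment.
2. State that Table 3 Stages 1–3 are also fitted to baseline FEER, with the Stage 3 autism and alexithymia coefficients as the test of the second aim.
3. Describe the match by the standardised difference in mean TAS-20 between groups, not by a significance test.
4. Make the covariate list under Statistical Analyses agree with Table 1 and the Discussion.

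The cost is one degree of freedom in the ANOVA and some wording. Both scales are already in the assessment schedule, the sample size stands, and the article reports that recruitment had not begun as of June 2021.

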**Methods:**

Recruitment will primarily take place through an ASD community group with emphasis put on snowball recruiting. Included will be 64 consenting adults equally divided between participants without an ASD and participants with an ASD. Participants will be screened online using the Kessler Psychological Distress Scale (K-10; cut-off score of 22), Autism Spectrum Quotient (AQ-10), and Toronto Alexithymia Scale (TAS-20) followed by a clinical interview with a provisional psychologist at the Federation University psychology clinic. The clinical interview will include assessment of ability, anxiety, and depression as well as discussion of past ASD diagnosis and confirmatory administration of the Autism Mental Status Exam (AMSE). Following the clinical interview, the participant will complete the Bermond-Vorst Alexithymia Questionnaire (BVAQ) and then undertake a baseline assessment of FEER. Consenting participants will then be assigned using a permuted blocked randomization method into either the control task condition or the mimicry task condition. A brief measure of satisfaction of the task and a debriefing session will conclude the study.

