## Introduction

### Background

Behavioral and cognitive neuroscience has elaborated a range of emotion-related difficulties with emotion recognition [1], empathy [2], and regulation of emotions in autism spectrum disorder (ASD) [3]. However, these abnormalities are not observed in all people with ASD [4]. Traditionally, these emotion-processing difficulties have been viewed as inevitable correlates of ASD, but recent research suggests that their presence is variable and better explained by co-occurring alexithymia. This suggestion is termed the alexithymia hypothesis [5] and is gaining significant support [6]. Alexithymia is a personality construct that relates to the inability to distinguish or describe the subjective feelings in the body produced by emotion. Alexithymia is related to both empathy [7] and emotion recognition [8] deficits. Severe degrees of alexithymia are manifested in up to 65% of adults with ASD [9].

The 2 forms of alexithymia, type 1 and type 2 [10], differ on the affective and cognitive dimensions [11]. Type 1 alexithymia includes high levels of both dimensions, whereas type 2 alexithymia only includes high levels of the cognitive dimension. Type 1 relates to reduced emotional reactivity (or a severe downregulation of emotional experience), and type 2 is typical emotional reactivity, but a reduced ability to interpret and describe that emotion [12].

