#### Bermond–Vorst Alexithymia Questionnaire

The Bermond–Vorst Alexithymia Questionnaire (BVAQ) [11] is also a measure of alexithymia that aims to assess the alexithymia construct more comprehensively across 2 subdimensions, namely the cognitive and the affective. Measuring these 2 subdimensions aids in distinguishing between participants with type 1 and type 2 alexithymia. In total, there are 40 items rated on a 5-point Likert scale, with higher scores indicating higher levels of alexithymia. This model of alexithymia and the BVAQ have demonstrated strong validity and reliability [10,11].

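### The ASD and AM groups are matched on one fallible screening TAS-20, so true alexithymia is expected to stay lower in AM, and the stated ANOVA covariates do not address it

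*Protocol article*

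**What the plan says.** Under Participants, the matching rule is that "the number of participants in each group meeting criteria for alexithymia will be matched as indicated by TAS-20 scores ≥61". Under Assessments, the TAS-20 is completed at the online stage, and "participants will be prescreened online to facilitate creating this composition of participants". So one screening score both steers who enters the AM group and defines the match. The TAS-20 section reports "an internal consistency of α=.81 and test-retest reliability of .77". The Background states: "Severe degrees of alexithymia are manifested in up to 65% of adults with ASD". No general-population rate, mean or SD is given.

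A second alexithymia scale is taken after selection: following the interview, "the participant will complete the Bermond-Vorst Alexithymia Questionnaire (BVAQ) and then undertake a baseline assessment of FEER". Table 1 places the TAS-20 under eligibility and the BVAQ under control variables. The BVAQ section gives its purpose this way: "Measuring these 2 subdimensions aids in distinguishing between participants with type 1 and type 2 alexithymia".

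Under Statistical Analyses, the ANOVA covariates are IQ, depression and anxiety. Comparability of the groups is to be tested on participant characteristics that are not named. Table 3 enters Autism and then Alexithymia in a hierarchical regression, without saying which instrument supplies the alexithymia term. The last two hypotheses, on improvement and on baseline recognition, expect no significant ASD-AM difference given the match on alexithymia.

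**The concern.** Matching on a score measured with error does not match the underlying trait when the two source populations differ in mean. A general-population volunteer with a high TAS-20 is more likely to owe part of it to a chance upward error than an ASD participant with the same score, because the score is more unusual in the first population. On average the AM volunteer's true level is the lower of the two.

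The second aim and the fourth and fifth hypotheses read the ASD-AM contrast as free of alexithymia because of the match. If residual alexithymia remains in the ASD group, a baseline recognition deficit produced by alexithymia alone would be read as an effect of autism. That is the opposite of what the alexithymia hypothesis says. For improvement scores the same imbalance carries over through whatever relation alexithymia has with improvement; the third hypothesis does not fix the sign of that relation.

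**Working it through.** **The plan's own figure.** With f² = 0.27, alpha 5% and six predictors (Table 3 has six terms), the overall regression test has power 0.808 at N = 58. This agrees with the stated 58, and 58 × 1.1 gives about 64. The sample size is not in question here. The protocol gives no figure for the quality of the match.

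**Inputs from the protocol.** Test-retest reliability .77 (alpha .81); up to 65% of ASD adults severely alexithymic; cut-off 61; about 32 per group.

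**Assumptions not in the protocol.** General-population share at or above 61 of 5 to 20% (10% central); correlation of alexithymia with recognition of 0.3 to 0.5; normal scores with equal SDs; 65% taken as the ASD share at or above 61, although it is stated as an upper limit.

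**Step 1: shortfall under exact score matching.** With E[true | observed x] = μ + ρ(x − μ) in each group, the groups at equal x differ by (1 − ρ)(μ_ASD − μ_AM). With ρ = .77 this is 23% of the source gap.

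| ASD share ≥61 | AM source share ≥61 (assumed) | Source gap (SD) | × 0.23 (SD) |
|---|---|---|---|
| 65% | 10% | 0.385 + 1.282 = 1.67 | 0.38 |
| 65% | 5% | 0.385 + 1.645 = 2.03 | 0.47 |
| 50% | 20% | 0 + 0.842 = 0.84 | 0.19 |

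Letting the ASD share fall to 40% and reliability rise to .81 widens the range to 0.11 to 0.47 SD.

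**Step 2: the rule as written.** Equal counts at 61 or above do not equalise scores within the two bands. In simulation at 65% v 10%, observed TAS-20 means still differ by 0.59 SD and true means by 0.84 SD. Over ASD 40 to 65% and AM 5 to 20%, the true difference is 0.32 to 1.03 SD. Exact matching is therefore the favourable case.

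**Step 3: effect on baseline recognition, exact matching, no true ASD effect.** Spurious d = r × 0.383/√.77 = 0.13 at r = .3 and 0.22 at r = .5. A two-sample t test at 32 v 32 then rejects in about 8% and 14% of trials instead of 5%. At the low end (0.19 SD, r = .3) it rejects in 5.8%. A simulation with AM scores paired to ASD scores gave 7.9% and 10.8%, against 2.7% with an error-free TAS-20 (run at r = .5).

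**Step 4: what adjustment can do (r = .5, central case).** The unadjusted group effect is −0.22 SD. Adjusting for the screening TAS-20 leaves −0.22, because under exact matching the groups already agree on it. Adjusting for a later measure with independent error and reliability q leaves about (1 − q) of the bias when the spread of true scores is not narrowed: 0.40 × 0.22 = 0.09 at q = .60, 0.23 × 0.22 = 0.05 at .77, and 0.15 × 0.22 = 0.03 at .85. A separate simulation was less favourable: −0.11, −0.07 and −0.05. On that less favourable account, about half to four-fifths of the bias is removed. The BVAQ section gives no reliability figure, so q is assumed.

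**Step 5: what a check of the match can show.** At 32 v 32 the 95% CI half-width for a standardised difference is 2.0 × √(2/32) = 0.50 SD. Power to detect 0.38 SD is about 32%.

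**The case against.** Several points on the other side stand.

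- **The BVAQ may already be intended for this.** A reader might infer that it plays no part in the analysis. The protocol does not support that: Table 1 makes it the only alexithymia scale among the control variables, the Table 3 term could be the BVAQ, and the comparability tests could include it. What can be said is that no such use is stated for the ASD-AM contrast or the match. The ANOVA covariates are listed by name, and no alexithymia measure is among them.
- **A TAS-20 comparison need not look balanced.** A reader might infer that it is balanced by construction. It is not: only counts at 61 are equated, and observed means could differ visibly (0.59 SD in the central case).
- **A BVAQ comparison would often miss the gap.** With about 32% power for 0.38 SD, a non-significant result would be false reassurance.
- **The BVAQ is no clean remedy.** It is fallible, its error may not be independent of the TAS-20's, and it covers an affective dimension, so a group difference on it could partly reflect content.
- **The size rests on assumptions.** The prevalences and the correlation with recognition are assumed. The distress and mental-health exclusions could change the source gap.
- **The Discussion partly concedes the inference.** It says matching may bring in other confounders and limits attribution to ASD or alexithymia. It does not mention measurement error, and it still presents the design as controlling for alexithymia.

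These points limit the claim. They do not remove the expected shortfall or the gap in the stated covariate set.

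**Conclusion.** The point holds as an expectation. It would go too far to say that the AM group certainly has lower true alexithymia: that depends on a lower mean in its source population, which is plausible but not documented. Given that, the shortfall is 23% of the source gap under exact matching, about 0.2 to 0.5 SD under the assumed prevalences, and larger under the count-only rule.

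The consequence is moderate. Under exact matching it is a spurious baseline ASD deficit of about 0.13 to 0.22 SD in the central case. The bias runs against the protocol's own no-difference hypotheses. It touches the second aim and the fourth and fifth hypotheses; its size for improvement scores has not been worked out. The mimicry-control comparison is randomised and is unaffected. The change is worth making because the data are already to be collected and the cost is very small.

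**What to change.** In Statistical Analyses:

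1. Add the BVAQ score as a covariate in the ASD-AM comparisons for the fourth and fifth hypotheses.
2. Name the BVAQ as the alexithymia term in Table 3.
3. Report the ASD-AM difference on the BVAQ and on the continuous TAS-20, each with a 95% CI, and do not treat a non-significant difference as proof of a match.
4. State that adjustment for the BVAQ reduces but does not remove the bias, because the BVAQ is itself fallible and also covers an affective dimension.

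The cost is one error degree of freedom and some wording. No new data are needed, since the BVAQ is already completed before baseline recognition is assessed.
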